### 2.8. Intervention

When the extremely premature infant is hemodynamically stable and one of the parents is staying at the NICU, the patient will be randomized into two groups: an experimental group or a control group. Said group allocation will be maintained along the first five days of life when KC will be performed (Figure 1. Flow of participants).

In the experimental group, KC lateral position will be performed. Premature infants will stay in between the mother’s breasts or father’s chest, in the upright position and side-lying, providing maximal skin-to-skin contact, with the limbs, arms, and legs bent to the midline. (Figure 1).

In the control group, KC prone position will be performed, so the baby will be placed in the upright position between the mother’s breasts or father’s chest and in a ventral position with its head to the side (90°), slightly extended to free the airway and to encourage visual contact between the mother/father and their child (Figure 1).

All infants in kangaroo care will be inside the polyethylene bags (NeoHelp TM^®^ (Vygon, Padova, Italy) to bring humidity into the environment and decrease hypothermia risk in the way we are reducing heat loss avoiding skin evaporation. The infant’s head will be covered, but keeping the skin-to-skin contact so that in the prone position, the bag will be open in the anterior side of the baby, and in the lateral position, it will be open in its lateral side.

The transfer will be done by the mother/father or the nurse. Nevertheless, during transfer, staff will always be present to ensure the safety, as well as the correct handling and fixing of lines, wires, and circuits, making sure everything is correct once the transfer is finished.

During KC sessions, we will provide comfort and privacy to the families. Parents will sit down in a reclinable armchair during KC. The study is carried out in a mixed allocation NICU where we have single-family rooms (with glass doors that allow staff to have a direct viewing from outside) and an open bay setting.

Participants in single-family rooms are monitored continuously through a central monitoring system which is controlled by NICU staff, alarms limits are set, and the direct view from outside is possible. Beyond this, parents can ring the bell in case they need to ask for help.

Premature infants’ axillary temperature will be assessed during kangaroo care. In the event of axillary temperature <36.5 °C, checks will be conducted to ensure the temperature sensor is placed correctly, adding a towel or blanket to the polyethylene bags covering it. The temperature will be reassessed after 15 min, adding another towel or blanket if it remains <36.5 °C. It will be assessed for the third time after 15 min, and kangaroo care will be suspended if the temperature remains <36.5 °C.

If during this time the neonate should have an axillary temperature >37.5 °C, the cover material (towel or blanket) will be gradually removed.

KC sessions can be at any time of the day, with the frequency and duration required by the mother/father, based on a minimum of 60 min. All KC sessions during the first five days of life will be monitored, recording data in the medical record, which will later be extracted and systematized in the study data collection notebook for analysis.

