### 2.5. Sample Size

The primary outcome was the neonatal body temperature difference between KC prone position and KC lateral position. The sample size was calculated to achieve an 80% statistical power with an α of 0.05 to detect a 0.3 °C difference in the body temperature (DS 0.16) [5,13], and the non-inferiority margin was set at a 0.2 difference in body temperature [13]. In addition, we estimated a 10% loss to follow-up, so the sample size calculated is 35 participants in each group.

Additionally, the sample size was calculated to the secondary outcome; it was the difference in neonatal pain level between KC prone position and KC lateral position. With the same power an α to detect 0.83 points (DS 1), the non-inferiority margin was set at 1.53 points in PIPP-R, and we estimated a 10% loss, the sample size calculated is 29 participants in each group [5].

Given the scarce and heterogenous literature available on IVH [24], the populational behavior of this variable is unknown, with no references to calculate the sample size.

Therefore, the minimum estimated sample size to respond to the aims proposed is 35 subjects in each group.

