The following independent variables will be obtained from each participant in every KC session:Demographic variables: gestational age at birth, gender, and birth date.Clinical data: Apgar score (test to assess the extrauterine adaptation of the newborn 1, 5, and 10 min after birth), type of delivery (eutocic, instrumental, cesarean), birth weight, gestational age, actual weight, hours of life, pathology at five days of life, analgesia administered (drug, route, dose and time since the last dose), painful/stressful procedures during kangaroo session, respiratory support (support type and fraction of inspired oxygen).Hemodynamics-related: maximum heart rate and minimum peripheral oxygen saturation observed for 20 s, apneas. Continuous hemodynamic monitoring to measure the heart rate, peripheral oxygen saturation, and apnea with Philips IntelliVue MP60/MP70^®^ monitor (Koninklijke Philips Electronics N.V., Eindhoven, Netherland) or Masimo SET^®^ oximetry monitor (Masimo, Irvine, CA, USA).Temperature-related: Giraffe ^®^ (GE Healthcare, Chicago, IL, USA) incubator air temperature and humidity; temperature and humidity of room or open-bay setting, where neonate is located assessed by Multi-Function Environment Meter PCE EM882 (PCE, Durham, United Kingdom), and temperature of humidifier chamber Dräger VentStar^®^ (Dräger, Lubeca, Germany).Kangaroo care: position (prone or lateral), date of KC session, session number, duration, KC provider (mother/father), axillary temperature of KC provider, materials used for kangaroo care, person transferring neonate.Environment room or open-bay setting: light and sound in macroenvironment assessed by Multi-Function Environment Meter PCE EM882, and activity inside the box room or open-bay setting with scale NIDCAP Nursery Certification Program [32].Adverse events or incidents: accidental removal of the line, such as umbilical venous or arterial catheters, venous catheter, or endotracheal tubes.The long-term outcomes we have collected are the number of days in NICU stay, the total number of days in the hospital, the number of days on mechanical ventilation, and mortality.The patient’s medical history will be used for the collection of demographic, clinical, and intraventricular hemorrhage (IVH)-related data. And the direct observation for measuring pain, activity inside the room or open-bay setting, and rest of outcome. They will be extracted and transferred to the data collection notebook.

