### 2.13. Statistical Analysis

Normality associated with each quantitative variable will be analyzed using the test Kolmogorov–Smirnov test.

A descriptive analysis will be performed of the demographic and clinical characteristics of subjects in both treatment groups: quantitative variables will be described by mean or median and their dispersion measurements, standard deviation or interquartile range, respective, as appropriate. Qualitative variables will be described by absolute frequencies and percentages. The descriptive analysis will be accompanied by the 95% confidence interval.

Prior to testing hypotheses, we will check whether both groups are homogeneous in terms of the baseline characteristics, using Student’s *t*-test or Mann–Whitney U for quantitative variables or ANOVA or Kruskal–Wallis if the variable does not follow normal distribution, and if statistically significant differences are found, we will continue with post hoc Bonferroni contrasts or weighted comparisons with Mann–Whitney U. Chi-squared will be used for qualitative variables.

If the groups are heterogeneous, confounding factors will be defined to adapt the final analysis to the main variable.

The effectiveness of KC modified lateral position compared to the KC conventional prone position will be assessed, calculating axillary temperature variation (Student’s t-test or Mann–Whitney U), level of pain (Student’s *t*-test or Mann–Whitney U), and IVH development (Chi-squared) in both groups.

Intention to treat (NNT) and protocol analyses will be performed. Should the results be conflicting, protocol deviations and/or breaches will be analyzed.

Safety analysis in relation to adverse events will be calculated using Pearson’s Chi-squared test or Fisher’s exact test as appropriate.

An explanatory model with stepwise linear regression will be created based on a significance level of 0.1, and confounding variables and their level of importance will be determined.

The statistical significance level will be *p* < 0.05. Data will be analyzed with the Statistical Package for the Social Sciences-IBM SPSS^®^ program version 25.0 (IBM, Chicago, IL, USA).

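### Every kangaroo care session goes to analysis, but only independent-observation tests are named and no per-infant value is defined; if sessions or readings are pooled, false non-inferiority becomes more likely

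*Protocol article*

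**What the plan says.** All references are to the protocol article.

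- **Randomised unit (2.6, 2.8).** Each infant is randomised once, before the first session, and keeps the allocated position for the first five days of life.
- **Sessions (2.8).** Sessions take place "with the frequency and duration required by the mother/father", subject to a 60-minute minimum. "All KC sessions during the first five days of life will be monitored, recording data in the medical record"; the same sentence says the data are later extracted for analysis.
- **Readings (2.11, Table 1).** Infant temperature is scheduled at t0, t1, t2 and t4, with further t2' readings in sessions longer than 60 minutes. Pain is scored at t0, t2, t2' and t4.
- **Covariates (2.11).** They "will be obtained from each participant in every KC session", and include session number, duration and who provided the care.
- **Discarding (2.15).** A session that does not follow the protocol is dropped as a session.
- **Outcome (2.10).** The primary outcome is the infant's axillary temperature, with nothing further specified.
- **Analysis (2.13).** Position is assessed by "calculating axillary temperature variation (Student’s t-test or Mann–Whitney U), level of pain" being tested in the same way. A stepwise linear regression follows.
- **Sample size (2.5).** "the non-inferiority margin was set at a 0.2 difference in body temperature", and "we estimated a 10% loss to follow-up, so the sample size calculated is 35 participants in each group".

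**The concern.** A two-sample t-test, a Mann–Whitney test and an ordinary linear regression all require independent rows. The data sent to analysis are nested: readings within sessions, sessions within infants. The named tests fit only if each infant is first reduced to one value, and the article defines no such value.

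If sessions or readings were entered as rows, two things would follow. First, the test would treat correlated values from one infant as separate evidence, so the standard error would be too small. In a non-inferiority trial this is the unsafe direction, because a falsely narrow interval makes it easier to exclude the 0.2 °C margin. Second, infants with more usable sessions would carry more weight. That count may not be neutral: 2.8 suspends kangaroo care when low temperature persists, and 2.4 and 2.15 list hypothermia or a session under 60 minutes as grounds for removal. The number of usable sessions can therefore depend partly on the primary outcome.

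If infants are reduced to one value, the tests are sound, but their input is still open: first session or all sessions, t1 or t2, level or change from t0. That choice could then be made after the data are seen.

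**Working it through.** **1. The plan's own figure.** Inputs from 2.5: difference 0.3, SD 0.16, margin 0.2, α 0.05, power 80%, loss 10%. Sidedness is not stated; one-sided 0.05 is the reading that reproduces the result.

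n = 2 × [SD × (1.645 + 0.842) / (0.3 − 0.2)]² = 2 × [0.16 × 2.487 / 0.1]² ≈ 31.65 per group. Allowing for loss, 31.65 / 0.9 ≈ 35.2, against the stated 35 (36 if 31.65 is first rounded up to 32).

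So 35 is a count of infants with one value each. It contains no term for repeated measures. (That the assumed difference exceeds the margin is a separate matter.)

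**2. Effect of pooling sessions.** The article gives neither the number of sessions per infant (m) nor the within-infant correlation (ρ). Both are assumptions here, as is one-sided testing at 5%.

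Design effect: DE = 1 + (m − 1)ρ. Actual one-sided error of a pooled test = 1 − Φ(1.645 / √DE).

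| m | ρ | DE | Actual error (nominal 5%) |
|---|---|---|---|
| 5 | 0.1 | 1.4 | 8.2% |
| 5 | 0.3 | 2.2 | 13.4% |
| 5 | 0.5 | 3.0 | 17.1% |
| 5 | 0.6 | 3.4 | 18.6% |
| 10 | 0.1 | 1.9 | 11.6% |
| 10 | 0.3 | 3.7 | 19.6% |
| 10 | 0.5 | 5.5 | 24.2% |
| 10 | 0.6 | 6.4 | 25.8% |

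Worked line, m = 5 and ρ = 0.3: DE = 1 + 4 × 0.3 = 2.2; 1.645 / √2.2 = 1.109; 1 − Φ(1.109) = 0.134. The pooled standard error is 1/√2.2 = 67% of its true size.

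**3. Unequal session counts.** The table assumes equal counts. A simulation (4000 runs, 35 infants per arm, varying session counts, two-sided 5% t-test, no true difference) gave:

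| Mean sessions | ρ | Sessions pooled | One mean per infant |
|---|---|---|---|
| 5 | 0.1 | 12.5% | 4.7% |
| 5 | 0.3 | 23.6% | 4.7% |
| 5 | 0.5 | 33.4% | 5.0% |
| 10 | 0.1 | 20.1% | 4.9% |
| 10 | 0.3 | 38.2% | 4.9% |
| 10 | 0.5 | 49.0% | 5.5% |

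For comparison, the two-sided error with equal counts of 5 is 9.8%, 18.6% and 25.8% at the same correlations, so unequal counts make pooling worse. One value per infant holds the error close to 5%.

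**The case against.** The strongest reply is that nothing in the article says sessions or readings are the rows of the test. Infants are randomised, numbered and counted in the sample size, and 35 per group reproduces as an infant-level figure. Section 2.13 speaks of temperature variation, which could well be a change score per infant, and a t-test on one such score is valid. The phrase about every session introduces covariates rather than the outcome, and dropping sessions concerns adherence. A condensed article may also leave the reduction of repeated readings to a fuller document.

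Most of this stands. A reader might infer that the plan commits to pooling, that its standard errors are in fact too small, and that the most-held or fittest infants dominate the estimate. The document supports none of these as fact. All infants must be hemodynamically stable to enter, and session frequency is left to the parents. The sizes rest on assumed inputs, and few sessions with low correlation would give modest inflation. Section 3 itself expects that instability may prevent early sessions and that the first session may come only at about 20 hours of life.

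What does not stand is that this is only missing detail. Section 2.13 commits to particular tests, and those tests do not fit the repeated, unequal data that 2.8 sends to analysis unless a step is added that the article never describes. Session number, duration and care provider vary between one infant's sessions, so using them in the regression makes session-level rows a plausible reading, though not a proven one.

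**Conclusion.** The point holds in conditional form. The stated tests and the stated data do not match, and the unit of analysis is open. On one reading the primary analysis is invalid; on the other it is valid but has no defined input.

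If sessions were pooled, a nominal one-sided 5% error would become about 8% to 19% with 5 sessions per infant and correlation 0.1 to 0.6, and about 20% to 26% with 10 sessions and correlation 0.3 to 0.6. Session count, correlation and one-sided testing are all assumptions. The direction is not in doubt for any positive correlation with more than one session per infant: false non-inferiority becomes more likely. The primary conclusion depends on the choice, so it should be settled before any comparison by group.

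**What to change.** In 2.13, state that the infant is the unit of analysis, and replace the plain t-test or Mann–Whitney for temperature with one of the following:

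1. **Linear mixed model** on the readings taken during kangaroo care, with fixed effects for position, time point and t0 temperature and random intercepts for infant and for session within infant. Take the confidence interval for position from this model and compare it with the 0.2 °C margin. Say which t0 is used; only that of the first session precedes all care in the allocated position.
2. **One pre-specified value per infant**, for example the mean in-session temperature of the first session, adjusted for t0, with all sessions as supportive analysis. This also removes any weighting by number of sessions.

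State the chosen value in 2.10. Do the same for PIPP-R, and allow for clustering by infant in the regression.

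The cost is a few sentences and slightly more analysis work. No new data are needed, and SPSS 25, already named, fits mixed models. The 35 per group is unchanged provided that the SD of 0.16 is the between-infant SD of the chosen value; 2.5 should say so.

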### 2.9. Participant Timeline

The participant timeline is presented in Table 1: participant timeline.

### 2.10. Outcomes

Primary outcome:
Premature infant axillary temperature.

Secondary outcomes:
Neonatal pain level.Intraventricular hemorrhage number of events.

### 2.11. Data Collection Methods

See Table 1: Participant timeline.

The following dependent variables will be obtained:Premature infant axillary temperature measured continuously with the temperature probe fixed (AirLife^TM^ Infant Skin temperature probe (Vyaire Medical Inc, Chicago, IL, USA), Giraffe^®^ incubator (GE Healthcare, Chicago, IL, USA) on the axillary infant with adhesive tape (protect the infant skin with hydrocolloid tape before).

The axillary temperature will also be taken with a Braun^®^ PRT2000 (Braun GmbH, Kronberg, Germany) thermometer.

Neonatal pain level assessed by Premature Infant Pain Profiled Revised. PIPP-R is a multidimensional scale (it includes physiological, behavioral, and facial expression signs for the pain assessment) developed by Stevens B [29], is valid for assessing pain in full-term and preterm neonates during painful procedures. Scores range from 0 to 21; score minor to 7 is interpreted as no pain or minor pain. Studies validating the scale show a high correlation between PIPP and PIPP-R is not painful (R2 = 0.91, *p* < 0.0001) and painful (R2 = 0.98, *p* < 0.0001) procedures. Average applicability scores are 3.5–3.7 (average of 4 out of 5) [30].

●Intraventricular hemorrhage (IVH) assessed by cranial ultrasonography using Siemens AcusonX300 ^®^ ultrasound system (Siemens AG, Berlin, Germany):
○IVH presence: yes or no.○Grade [31]
-Grade 1: hemorrhage located in the subependymal germinal matrix.-Grade 2: intraventricular blood content occupies less than 50% of the intraventricular area.-Grade 3: blood occupies >50% and distends ventricle.-Grade 4: significant overdistension of lateral ventricles and the entire ventricular system in general.○Location: right, left, or bilateral.○Date of cranial ultrasonography.

Transfontanelar ultrasound will be performed at two different times, the first before the first KC session by a specialist in neonatology with specific training in neonatal ultrasound, under early IVH detection screening. The head US done before the first KC session is used as a control US to identify the presence of congenital HIV or bleeding on the first hours of life. This way, we can determine it is not associated with the kangaroo position in prone.

The second ultrasound at 48 h of life (according to the study unit protocol) by a specialist in radiodiagnosis.

The following independent variables will be obtained from each participant in every KC session:Demographic variables: gestational age at birth, gender, and birth date.Clinical data: Apgar score (test to assess the extrauterine adaptation of the newborn 1, 5, and 10 min after birth), type of delivery (eutocic, instrumental, cesarean), birth weight, gestational age, actual weight, hours of life, pathology at five days of life, analgesia administered (drug, route, dose and time since the last dose), painful/stressful procedures during kangaroo session, respiratory support (support type and fraction of inspired oxygen).Hemodynamics-related: maximum heart rate and minimum peripheral oxygen saturation observed for 20 s, apneas. Continuous hemodynamic monitoring to measure the heart rate, peripheral oxygen saturation, and apnea with Philips IntelliVue MP60/MP70^®^ monitor (Koninklijke Philips Electronics N.V., Eindhoven, Netherland) or Masimo SET^®^ oximetry monitor (Masimo, Irvine, CA, USA).Temperature-related: Giraffe ^®^ (GE Healthcare, Chicago, IL, USA) incubator air temperature and humidity; temperature and humidity of room or open-bay setting, where neonate is located assessed by Multi-Function Environment Meter PCE EM882 (PCE, Durham, United Kingdom), and temperature of humidifier chamber Dräger VentStar^®^ (Dräger, Lubeca, Germany).Kangaroo care: position (prone or lateral), date of KC session, session number, duration, KC provider (mother/father), axillary temperature of KC provider, materials used for kangaroo care, person transferring neonate.Environment room or open-bay setting: light and sound in macroenvironment assessed by Multi-Function Environment Meter PCE EM882, and activity inside the box room or open-bay setting with scale NIDCAP Nursery Certification Program [32].Adverse events or incidents: accidental removal of the line, such as umbilical venous or arterial catheters, venous catheter, or endotracheal tubes.The long-term outcomes we have collected are the number of days in NICU stay, the total number of days in the hospital, the number of days on mechanical ventilation, and mortality.The patient’s medical history will be used for the collection of demographic, clinical, and intraventricular hemorrhage (IVH)-related data. And the direct observation for measuring pain, activity inside the room or open-bay setting, and rest of outcome. They will be extracted and transferred to the data collection notebook.

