The possible limitations of the study are as follows: (a) in terms of the study population, due to the immaturity of the premature infants, the sample size may be reached in a broad period of time caused as possible hemodynamic instability may not allow kangaroo care the first days of life; (b) regarding intervention, the first kangaroo care session may be delayed until approximately 20 h of life due to the numerous formalities required of the father, and as the mother is normally not available to act as kangaroo due to health issues as she is not admitted in the same room as the baby; (c) related to biased information as the data collection notebook is not fully filled in due to healthcare team workload, always guaranteeing the collection of dependent variables; (d) ultrasound sensitivity in early intraventricular hemorrhage detection; (e) the relatively small sample size for the IVH outcome. The sample size for this secondary outcome was not calculated due to the heterogenous literature available about IVH in relation to the risk that would be caused by the prone position compared with the other positions; and finally, (f) pain is measured on the validated PIPP-R scale but not validated in Spanish; there is currently no validated scale in Spanish for assessing neonatal pain. In addition, with regard to the assessment of pain, it will not be possible to blind the observers or to carry out the measurement of pain by two professionals independently.

These restrictions will be taken into account during data analysis, analyzing missing values, and, if necessary, completing simple imputation of these values.

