## Figures and Tables

**Figure 1 ijerph-19-00293-f001:**
[figure not shown]
Flow of participants.

**Table 1 ijerph-19-00293-t001:** Participant timeline. SPIRIT Schedule of enrolment, interventions and assessment.

	Activity/Assessment	Staff Member	Approximate Time to Complete	Before First Session Kangaroo Care	t_0_	t_1_	t_2_	t_2_’	t_3_	t_4_	t_5_
enrollement	Informed consent	Study coordinator/study staff	10 min	x							
	Inclusion/exclusion form	Study coordinator/study staff	2 min	x							
	Allocation	Study coordinator/study staff	1 min	x							
Intervention	Intervention A: Prone kangaroo care	Neonatal nurse	5 min								
	Intervention B: Lateral Kangaroo care	Neonatal nurse	5 min								
	Eco-TF	physician	5–10 min	x							
Assessment	neonatal axillary temperature	Neonatal nurse	<1 min		x	x	x	x		x	
	Score pain	Neonatal nurse	min		x		x	x		x	
	Eco- TF: Intraventricular hemorrhage (IVH)	physician	5–10 min	x							x
	mother/father axillary temperature	Neonatal nurse	10 seg		x		x	x	x		
	Incubator temperature	Neonatal nurse	1.5 min		x					x	
	Incubator humidity	Neonatal nurse			x					x	
	Heater temperature	Neonatal nurse			x		x	x		x	
	Heart rate	Neonatal nurse			x		x	x		x	
	Oxygen Saturation	Neonatal nurse			x		x	x		x	
	Fio2	Neonatal nurse			x		x	x		x	
	Apnea				x		x	x		x	
	Box temperature	Neonatal nurse	1 min		x		x	x		x	
	Box humidity	Neonatal nurse			x		x	x		x	
	Sound	Neonatal nurse			x		x	x		x	
	Light	Neonatal nurse			x		x	x		x	
	Activity inside the box	Neonatal nurse	2 min		x		x	x		x	
	Duration kangaroo care	Neonatal nurse	<1 min								
	days in NICU stay	Study coordinator	5 min								x
	days in the hospital	Study coordinator	5 min								x
	days on mechanical ventilation	Study coordinator	5 min								x
	Mortality at 6 month old	Study coordinator	5 min								x

t_0_: 10 min previous the kangaroo care. t_1_: 15 min after beginning the kangaroo care. t_2_: 30 min after beginning the kangaroo care. t_2_’: if the duration kangaroo care is longer than 60 min, It assessment each 60 min after beginning the kangaroo care, so, 120 min after beginning the kangaroo care; 180 min after beginning the kangaroo care, etc. t_3_: at finish the kangaroo care. t_4_: 30 min after finish the kangaroo care. t_5_: delivery.

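### Section 2.11 and Table 1 disagree on when the IVH outcome is read, and the 48-hour reading would precede most of the five-day kangaroo care window

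*Protocol article*

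**What the plan says.** Section 2.11 of the protocol article plans two scans: "Transfontanelar ultrasound will be performed at two different times, the first before the first KC session". It gives that scan's purpose: "The head US done before the first KC session is used as a control US to identify the presence of congenital HIV" (evidently IVH is meant) or bleeding in the first hours, so that such bleeding is not attributed to the prone position. It then continues: "The second ultrasound at 48" hours of life, following the unit's own protocol. It mentions no later scan.

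The exposure lasts longer. Section 2.8 states: "Said group allocation will be maintained along the first five days of life when KC will be performed". It adds: "All KC sessions during the first five days of life will be monitored". The Abstract puts the IVH safety question for prone KC over the same five days.

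On when KC starts, the limitations in Section 3 note that "the first kangaroo care session may be delayed until approximately 20" hours of life, and that "possible hemodynamic instability may not allow kangaroo care the first days of life".

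Table 1 has no 48-hour column. Its row "Eco- TF: Intraventricular hemorrhage (IVH") is marked before the first session and at t5, and the footnote defines t5 as delivery.

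**The concern.** An outcome scan has to follow the exposure it is meant to judge. A 48-hour scan comes well before the end of a five-day exposure, and for a late starter it comes before any exposure. Table 1 points to a different time, but the label on that time cannot be right as written.

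Comparing IVH by assigned position is a stated secondary aim (Section 2.1). Section 2.15 also makes a rise in IVH in the control group the reason to halt the trial, checked at an interim analysis and again with every 20 new participants. If the scan is read at 48 hours, bleeds that arise later under the allocated position are not systematically looked for in either group. Infants not yet held contribute a reading that position cannot have affected. Both pull the comparison toward no difference, which here would be read as reassurance about prone KC.

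**Working it through.** The protocol gives no sample size, event count or power for IVH, so there is no planned figure to reproduce. The check is of timing only.

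**Inputs**
- Outcome scan under Section 2.11: 48 h of life.
- End of allocated KC (Section 2.8): five days of life, 5 × 24 = 120 h.
- Age at first session, *s*: Section 3 names about 20 h as a possible delay. It is not an expected value, so a range is shown.
- Limit on *s*: none before 48 h. Section 2.8 randomizes once the infant is stable and a parent is present, and the Abstract describes eligibility across the first five days.
- Period of higher IVH frequency (Introduction): first 72 h of life.

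**Share of the eligible KC window that follows a 48 h scan**

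Share = (120 − max(48, *s*)) / (120 − *s*)

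| First session, *s* | Hours after scan / window | Share after scan |
|---|---|---|
| 0 h | 72 / 120 | 60.0% |
| 12 h | 72 / 108 | 66.7% |
| 20 h | 72 / 100 | 72.0% |
| 24 h | 72 / 96 | 75.0% |
| 36 h | 72 / 84 | 85.7% |
| 48 h or later | all | 100% |

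For *s* at or above 48 h, the 48 h scan falls before or together with the control scan, so Section 2.11 schedules no reading after exposure.

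**Against the protocol's own risk period.** From a 20 h start to 72 h there are 72 − 20 = 52 h. The scan leaves 72 − 48 = 24 h of these unread: 24/52 = 46%.

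**Table 1.** The other t5 rows are days in the NICU, days in hospital, days on mechanical ventilation, and mortality at 6 months of age. None can be recorded at birth, so t5 appears to be a late time point such as discharge. Under that reading the second scan would normally follow the five-day window and the shares above would not apply. The two places therefore define different outcomes, and nothing in the article says which one governs.

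**The case against.** The strongest reply is that Table 1 already lists a later scan, so nothing is lost. A reader might infer from Section 2.11 alone that the outcome is settled at 48 h, or from the t5 label that Table 1 is meaningless. Neither holds. The timing is contradicted, not fixed, and the label looks like a slip. But t5 has no stated time, and Section 2.11 is explicit, so the reply does not remove the need to reconcile them.

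A reader might also take 72% as the share of KC, or of bleeds, that the scan misses. The documents do not support that. They give no KC hours per day, and the Introduction says IVH is more frequent in the first 72 h, so the share of bleeds missed may be well below the share of calendar time. The number of infants first held after 48 h is unknown.

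Nor would every later bleed be lost. Section 2.11 records the date of ultrasonography, and Section 2.19-type data are not needed to see this: the data collection text takes IVH data from the medical history and records pathology at five days. A bleed found clinically could be captured. That is not scheduled screening, so the fair description is incomplete ascertainment.

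Finally, a reader might infer that bleeds present before KC will be counted as outcomes. Section 2.11 states the opposite purpose for the control scan, Section 2.13 analyses the development of IVH, and an exact coding rule may sit in a document not shown.

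Section 3 does concede limited ultrasound sensitivity and a small sample for IVH. It does not mention scan timing.

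**Conclusion.** The point stands as a contradiction in the definition of a named secondary outcome. If Section 2.11 is followed, the IVH reading precedes 60% to 72% of the eligible KC window for first sessions between birth and 20 h, more for later starts, and all KC for infants first held at or after 48 h. This rests on a window ending at 120 h and on calendar hours. It would equal the share of KC itself only if sessions were spread evenly over the window, which the documents do not say.

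The direction of the effect is clearer than its size. IVH over the five days that the Abstract asks about would be incompletely ascertained, with a bias toward no difference between positions. The repeated safety looks in Section 2.15 would share this weakness. The number of bleeds affected cannot be estimated from the documents.

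**What to change.** 1. Reconcile Section 2.11 with Table 1 on the time of the outcome scan, and correct the t5 label.
2. Take the IVH outcome from the second scan already listed in Table 1, timed after the five-day KC period, and define it as new or worsened IVH relative to the pre-KC scan. Keep the 48 h unit scan as an intermediate reading.
3. State how deaths before the outcome scan are counted, for example by the last available scan after KC start, with death reported alongside.
4. If the 48 h scan remains the only outcome scan, restrict the IVH conclusion to exposure before 48 h, and do not count infants first held after it as having a post-exposure reading.

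The cost is wording, provided the t5 scan in Table 1 is done. Table 1 gives 5–10 min per scan. The downside is that, if that scan is not in fact done, a later routine scan would have to be used or the conclusion narrowed as in step 4.
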